## **Research Protocol**

### **A randomized controlled trial study of the use of transcranial direct current stimulation (tDCS) in treating dysarthria post-stroke**

#### **Background of research**

Dysarthria refers to neurological motor speech disorders resulting from disturbances in muscular control (e.g. paralysis, weakness or incoordination) over the speech mechanism [1]. Symptoms may be manifested in breathing, phonatory, resonatory, articulation and prosodic aspects of speech production [2]. Dysarthric speech may sound mumbled, choppy, soft, slurred, slowed but rushed, with abnormal pitch and rhythm [2]. As a result, dysarthria is associated with reduced speech intelligibility. Its impacts on oral communication can be chronic and debilitating and has the potential to significantly affect a patient's quality of life, which can lead to social isolation and depression. Stroke patients often demonstrate various types of motor speech problems. Previous studies have revealed that about 22-60% of stroke patients suffered a dysarthria [2, 3]. Treating dysarthria and improving their speech intelligibility therefore is an important part of post-stroke rehabilitation. Although research has indicated that the age-standardized mortality rate of stroke in Hong Kong is lower than the global rate and is declining [4], stroke is still a prominent cause of permanent disability in adults, affecting the person who may be disabled as well as their family and caregivers. With the rapidly ageing population in Hong Kong, it is expected that about one third of the population will be 60 years or older by 2050. Hence, stroke and stroke related disability would remain a significant disease burden in Hong Kong [5].

The commonly occurring features of dysarthria post-stroke including imprecision of articulation, slowed speaking rate, monotonous speech and voice disturbances [3]. Traditionally, speech therapy often involves strategies that focus on reducing the physiological impairment of a particular speech sub-system, for example, modifying the prosody and rate of speech to increase speech intelligibility, improving articulatory function for speech as well as articulation training [6, 7]. Some studies have used the Lee Silverman Voice Treatment, a treatment program reported to be effective in helping dysarthric individuals with Parkinson's disease to improve articulation and voice function in patients with dysarthria post-stroke [8, 9]. However, there is currently a paucity of rigorous scientific evidence supporting the efficacy of traditional treatment in the management of dysarthria post-stroke [3, 6].

In recent years, transcranial direct current stimulation (tDCS) has been widely used as a non-invasive brain stimulation technique to modulate cognitive functions and motor behaviour in healthy and brain-damaged individuals [10-15]. Compared with other brain stimulation techniques (e.g., transcranial magnetic stimulation), tDCS has the advantage of being noninvasive, portable and inexpensive. The procedure has also been found to be safe, with no evidence in neuronal damage checked with serum neuron-specific enolase [16, 17], MRI of edema in the related neurons [18], EEG waveforms [19], and thermal changes [20]. During tDCS intervention, a low amplitude direct current (typically between 0.5 and 2.0 mA) is transmitted through the scalp and skull to a specific cortical region via two electrodes (i.e., anode and cathode) placed on the scalp. The nature of the effect depends on the polarity of the current. Generally, an anodal (excitatory) tDCS increases neural excitability, whereas cathodal (inhibitory) tDCS decreases neural excitability [16]. The mechanism of tDCS is relatively well understood. Physiologically, the presence of the direct current (electrical

potential) in the region alters the polarization characteristics of the neurons. According to the literature, it is believed that the neurons near the anode (positive pole) are excited, with resting membrane potential shifting towards depolarization and an increased rate of spontaneous neuronal firing. On the contrary, neurons near the cathode (the negative pole) are inhibited, with resting membrane potential shifting towards hyperpolarization and a reduced rate of neuronal firing [21, 22]. As a result of the change in polarization behaviour of the neuronal cells, various functions can be altered. Research in healthy individuals showed that anodal tDCS enhances motor learning [23] and visuomotor performance [24] as well as improves working memory [25], verbal fluency [26] and vocal reaction times [27]. On the other hand, cathodal tDCS may reduce performance in working memory task [28] or may not have significant effect on a learning task [23].

Over the years, the application of tDCS in the management of psychiatric diseases [29] and neurological diseases, including stroke, has been increasing [15]. Research showed that tDCS has the potential to modulate motor recovery [11, 12, 30, 31] and language rehabilitation in aphasia post-stroke [32-35]. In the domain of speech production, recent reports have highlighted the beneficial effects of anodal tDCS in speech repetition tasks. In a preliminary study, Marangolo, Marinelli [36] applied 20 minutes of anodal tDCS over the left inferior frontal gyrus of three chronic aphasic patients while performing a speech repetition task. The tDCS stimulation, together with language therapy, was delivered for five consecutive days. Greater response accuracy was reported following the anodic stimulation. Similar positive effects on articulation were reported in another study with eight chronic patients who underwent bihemispheric stimulation over the left and right frontal regions together with concurrent speech therapy [37]. Significant recovery as indicated by better accuracy and speed in speech articulation were documented.

However, the application of tDCS in the management of dysarthria post-stroke has been limited. To the investigators' knowledge, only one study had investigated the effect of tDCS in the management of dysarthria post-stroke [38]. tDCS and conventional speech therapy were delivered to six acute stroke patients with dysarthria for a total of 10 sessions over a two-week period. Beneficial effects of anodal tDCS in treating dysarthria were reported. Despite the reported positive effects of tDCS, the observed improvement may have been contributed by spontaneous recovery. Moreover, the inclusion of a very small number of patients in the study also limited the generalization of the findings of the study. Therefore, more studies are needed to evaluate the efficacy and effectiveness of tDCS in the treatment of dysarthria post-stroke.

The current proposal is guided by evidence that anodal tDCS has the ability to modulate motor recovery and speech production in stroke [11, 38]. Since dysarthria is a disorder of speech movement resulting from disturbances in muscular control over speech mechanism [2], anodal tDCS to the motor area may potentially be used as an additional treatment in the management of dysarthria post-stroke. Research also showed that the electrophysiological effects of tDCS would outlast the duration of stimulation by up to 90 minutes after sessions of 1 mA polarization lasting for 9 - 13 min [23, 39, 40] and up to 2 months after 5-10 sessions of 1mA anodal stimulation lasting for 20 minutes [35, 36].

In an effort to confirm the ability of tDCS in the enhancement of speech motor performance, a pilot study was carried out by PI and Co-Is to investigate the short term effect of anodal tDCS. The study aimed at examining the possible effect in enhancing articulatory skills in performing tongue twister production task in healthy individuals who are native speakers of

Cantonese. Seven university students aged 18-25 years old with normal hearing participated in the study. All participants were native speakers of Cantonese who have no history of speech disorders, language disorders, brain surgery, seizure or stroke, and any implanted electrical or metallic device in the body.

Anodal tDCS was delivered to F5 region of the extended International 10-20 system for EEG electrode placement, which corresponds best to Broca's area [41]. A mild direct current of 2 mA was delivered to each participant by using a constant direct current stimulator (Chattanooga Ionto, Salty Lake, US) via saline-soaked sponge electrodes (50 x 70 mm) (EasyPads, Soterix Medical Inc., New York, USA) for 15 minutes [42]. For each participant, baseline data were obtained 30 minutes before the tDCS began. The participants were required to produce ten tongue twisters as fast and accurately as possible. During the recording the tongue twisters were presented in a random order using a computer. To avoid learning effect, no practice was provided prior to the experiment. Immediately after the stimulation, the participants were presented with the same tongue twisters and they have to produce them as fast and accurately as possible. Simultaneous to the tongue twister production by the participants, acoustic signals were recorded using a high-quality microphone (SM59A, Shure, USA) and a pre-amplification system (USB Pre, M-Audio, USA). A sampling frequency of 44 kHz and quantization rate of 16 bits/sample was used. Response accuracy and vocal reaction times in producing each tongue twister was collected for before, immediately after and 3 hours after the stimulation. Outcome measures included percent articulation accuracy (calculated by dividing the number of words correctly pronounced by the total number of words x 100%). In addition, acoustic analysis allowed calculation of perturbation measures such as jitter (perturbation in fundamental frequency), and shimmer (perturbation in amplitude). Average speech rate values (in WPM) were also obtained by dividing the number of words with the total time lapsed. To assess the reaction time, vocal reaction time values were also calculated from the onset of the presentation of visual stimulus to the offset of the participant's response.

The various measurements were obtained three times: 30 minutes before tDCS (pre), immediately after tDCS (post 1) and 3 hours after tDCS (post 2). While data are still being analyze statistically, preliminary findings in both articulation accuracy and vocal reaction time consistently indicate improved articulation through tDCS. In particular, nonparametric Friedman test revealed that the average vocal reaction time values obtained after stimulation were significantly shorter than before stimulation (pre = 10.405, post1 = 8.085, & post2 = 7.948) ( $p < 0.01$ ), with no significant difference between post1 and post2 measurements. Although accuracy measure showed no significant difference ( $p > 0.05$ ), the average accuracy values were steadily increased from 7.19 (pre) to 8.19 (post1) to 8.76 (post2). In sum, anodal tDCS over the left frontal region including Broca's area (F5) can enhance the accuracy and reaction time of tongue twister production in healthy individuals and the effect was maintained immediately after the stimulation.

### **The goal of the proposal project**

The aim of the proposed study is to examine the short-term and long-term effects of tDCS on speech intelligibility and speech related physiological functions in chronic stroke patients who suffered a dysarthria. The ultimate goal of this project is to understand the mechanism of tDCS-induced effects, its application to the current models of motor speech rehabilitation post-stroke as well as to determine if tDCS can be used as an additional treatment approach targeting dysarthria post-stroke. It is anticipated that tDCS is effective in helping stroke patients with dysarthria in improving their speech production, thus their intelligibility and

eventually their quality of life after stroke. In addition, the proposed study will examine the change in speech motor function by using a comprehensive array of perceptual, acoustical, kinematic, and physiological measurements.

It is hypothesized that, given the proven ability of tDCS to increase the cortical excitability in individuals post-stroke, tDCS to the orofacial area of the primary motor area (SM1) of the affected hemisphere would result in increased speech intelligibility and speech related physiological functions.

## **Research plan and methodology**

### **Participants**

Participants will include 60 adults who are at least 6-month after their initial stroke and have suffered a dysarthria post-stroke. Based on the study by You, Chun [38] with an effect size of 1.08, priori power analysis showed that at least a total of 40 participants (20 participants in each group) are needed. Taking into account an attrition rate of around 25%, the minimum sample size for this study is 50 participants. The requirement of 6 months post stroke is to avoid possible spontaneous recovery effect. As sex does not appear to be a factor in the study, both male and female participants will be recruited. Participants will be recruited from Queen Mary Hospital and Tung Wah Hospital. Standard inclusion/ exclusion criteria for speech research and exclusion criteria for tDCS as will be adopted in the proposed study. Individuals with a personal or family history of epilepsy or seizures; a history of a neurological condition, speech disorders, oro-maxillo-facial surgery involving the tongue and/or lip, severe cognitive impairment, severe aphasia, in an unstable or serious medical condition including heart disease, metallic foreign body implant and/or any medications that lower neural thresholds (e.g. tricyclines, antidepressants, neuroleptic agents, etc.) will be excluded from the study. All participants will be screened using Cantonese mini-mental state examination (MMSE) and speech and language screening to exclude patients with cognitive impairment, aphasia and apraxia of speech.

### **Methods**

#### ***Definition and classification of dysarthria***

Each participant will be required to read a standard Chinese paragraph to generate a speech sample. Five experienced speech-language pathologists, who are blinded to the neurological condition and history of each participant will analyze the speech samples independently using a Hong Kong-based perceptual rating scales devised by Whitehill, Ma, and Lee [43]. The rating scale includes 21 speech dimensions covering eight categories, including pitch, loudness, voice quality, resonance, rate, articulation, tone, and general impression. The speech samples will be rated using a seven-point equal-appearing interval scale. During the process of rating the speech samples, the speech-language pathologists will determine the presence, type and severity of any associated dysarthria based on the Mayo Clinic model [2]. In cases of discrepancies, the speech-language pathologists will discuss among themselves and produce a single consensus rating to be used in all further analysis.

#### ***Transcranial direct current stimulation***

High-definition tDCS will be applied in 10 daily sessions during a 2-week period, administered on Monday to Friday. The anodal stimulation will be delivered to the primary motor cortex (SM1) of the orofacial area. Previous studies have reported that up to 2 mA DC stimulation can be safely applied over the human cortex for up to 20 minutes [42]. As such, the current strength selected for this study will be 2 mA and the stimulation will last for 15 minutes. For the sham tDCS group, the same setting of tDCS electrodes will be applied on the scalp, but the stimulation will only last for 30 sec in order to cause similar sensation on

the scalp as the other group.

The conventional tDCS is performed using large electrode pads, most commonly between 25-35 cm^2, which stimulates relatively broad areas of cerebral cortex located between the anode and cathode pads. Therefore, focal stimulation of the target cortical region, not involving stimulation of neighbouring anatomical areas, is difficult to achieve with this conventional diffuse tDCS technique. However, increased focality would be desirable in applying tDCS on post-stroke patients. First, it may help achieve beneficial clinical effects with larger effect sizes. Second, it may also contribute to the understanding of the specific cortical regions implicated in therapeutic action, which is difficult to dissect with conventional diffuse tDCS. Finally, a more focal intervention may also be associated with increased safety. It could potentially reduce the likelihood of side effects due to decreased stimulation of adjacent regions, thus allowing for stimulation with increasing intensity or repletion to enhance efficacy.

### ***Speech and voice therapy***

For both anodal stimulation group and sham stimulation group, standard speech and voice training will be delivered to the participants. The treatment targets will be chosen based on the speech assessment results and will include drilling of speech production and voice rehabilitation. Each therapy session will be carried out simultaneously as the tDCS stimulation and will be within 30 minutes. Other than the designated period, the participants should have received no other speech and voice therapy.

### ***Study design***

The proposed project will be a randomized, placebo-controlled double-blinded control study. Following recruitment, the participants will be randomly assigned to one of two groups: Group 1 (n = 30) will receive anodal tDCS stimulation and intensive speech and voice therapy; Group 2 (n = 30) will receive sham tDCS stimulation and intensive speech and voice therapy. Both objective and subjective measurements on speech and speech-related physiological function will be administered four times in this study. The data collection will include perceptual and acoustic measurements, kinematic measurements, strength and endurance measurements and dysarthria-related quality of life measurements. The assessment will be conducted prior to tDCS baseline, immediately post tDCS, and post tDCS at 1-month and 3-month to assess the treatment outcome.

### **Data processing and analysis**

#### ***Primary outcome measure***

##### ***Perceptual and acoustic speech assessments***

All participants will be required to produce a sustained vowel /a/, repeat some syllables (i.e., /pa/, /ta/, /ka/ and /pataka/), read a standard paragraph in Cantonese and have a two-minute conversation with the investigator. A professional grade microphone (SM58, Shure, USA) will be placed 10 cm in front of the participant's mouth to ensure the quality of recording from the interference of airbursts. Each task will be repeated five times for recording. The voice samples will be recorded by using a preamplification unit (MicroBook II, Motu, USA). The medial portion of the three trials will be selected for acoustic analysis using the PRAAT software, a signal analysis software suite.

For perceptual speech rating, five experienced speech-language pathologists blinded to the neurological condition and history of each participant will analyze the speech samples independently using the perceptual rating scales adopted by Whitehill, Ma [43]. The rating

scales include 21 speech dimensions covering eight categories, including pitch, loudness, voice quality, resonance, rate, articulation, tone, and general impression. The speech samples will be rated using a seven-point equal-appearing interval scale. During the process of rating the speech samples, the presence, type and severity of any associated dysarthria will be determined based on the Mayo Clinic model [2]. In cases of discrepancies, the speech-language pathologists will discuss among themselves and produce a single consensus rating to be used in all further analysis.

Acoustic analysis will be carried out using the PRAAT software. Acoustic measurements will include fundamental frequency (F0), variability of fundamental frequency (vF0), frequency perturbation (jitter %), intensity perturbation (shimmer %), relative average perturbation (RAP), and noise to harmonic ratio (NHR) to be obtained from both sustained vowel phonation and connected speech.

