### **Statistical analyses**

Two-way repeated-measures Analyses of Variance (ANOVAs) will be applied for each dependent variable. Post-hoc multiple comparisons will be carried out when necessary.

1. Darley, F.L., A.E. Aronson, and J.R. Brown, *Differential diagnostic patterns of dysarthria*. Journal of Speech and Hearing Research, 1969. **12**: p. 246-269.
2. Duffy, J.R., *Motor speech disorders: Substrates, differential diagnosis, and management*. 3rd ed. 2013, St. Louis, MO: Elsevier Mosby.
3. Mackenzie, C., *Dysarthria in stroke: A narrative review of its description and the outcome of intervention*. International Journal of Speech-Language Pathology, 2011. **13**(2): p. 125-136.
4. Ng, P.W., *The stroke epidemic*. Hong Kong Medical Journal, 2007. **13**: p. 92-94.
5. Woo, J., et al., *Stroke incidence and mortality trends in Hong Kong: Implications for public health education efforts and health resource utilisation*. Hong Kong Medical Journal, 2014. **20**(Supplement 3): p. S24-29.
6. Yorkston, K.M., et al., *Evidence for effectiveness of treatment of loudness, rate, or prosody in dysarthria: A systematic review*. Journal of Medical Speech-Language Pathology, 2007. **15**(2): p. xi-xxxvi.
7. Yorkston, K.M., et al., *Management of motor speech disorders in children and adults*. 2nd ed. 1999, Austin, Texas: Pro-Ed.
8. Wenke, R.J., P. Cornwell, and D.G. Theodoros, *Changes to articulation following LSVT® and traditional dysarthria therapy in non-progressive dysarthria*. International Journal of Speech-Language Pathology, 2010. **12**(3): p. 203-220.
9. Wenke, R.J., D. Theodoros, and P. Cornwell, *The short- and long-term effectiveness of the LSVT® for dysarthria following TBI and stroke*. Brain Injury, 2008. **22**(4): p. 339 - 352.
10. Flöel, A., *Non-invasive brain stimulation and language processing in the healthy brain*. Aphasiology, 2012. **26**(9): p. 1082-1102.
11. Adeyemo, B.O., et al., *Systematic review of parameters of stimulation, clinical trial design characteristics, and motor outcomes in non-invasive brain stimulation in stroke*. Frontiers in Psychiatry, 2012. **3**(88).
12. Kim, D.-Y., et al., *Effect of transcranial direct current stimulation on motor recovery in patients with subacute stroke*. American Journal of Physical Medicine & Rehabilitation, 2010. **89**(11): p. 879-886.

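### The protocol's single primary outcome is a block of 33 variables, each with its own ANOVA, and no variable, visit or between-arm contrast is designated to test the intelligibility part of the hypothesis

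*Protocol*

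**What the plan says.** Protocol, Data processing and analysis, has a section headed Primary outcome measure, in the singular. Its only content is the block Perceptual and acoustic speech assessments, which has two parts:

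- Perceptual: the rating "scales include 21 speech dimensions covering eight categories, including pitch, loudness, voice quality, resonance, rate, articulation, tone, and general impression", each on a seven-point scale.
- Acoustic: six measures (F0, its variability, jitter, shimmer, RAP and NHR), "to be obtained from both sustained vowel phonation and connected speech".

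Statistical analyses consists of two sentences: "Two-way repeated-measures Analyses of Variance (ANOVAs) will be applied for each dependent variable" and "Post-hoc multiple comparisons will be carried out when necessary".

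The goal of the proposal project hypothesises that stimulation "would result in increased speech intelligibility and speech related physiological functions".

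Study design sets four assessments: "The assessment will be conducted prior to tDCS baseline, immediately post tDCS, and post tDCS at 1-month and 3-month to assess the treatment outcome". None is called primary.

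Participants bases the power analysis on one earlier study "with an effect size of 1.08" and arrives at 20 per group. It does not name the outcome behind that effect size, nor the alpha, sidedness or power.

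**The concern.** Identifying the primary outcome is the protocol's task. This Protocol does identify it, but as a block of undifferentiated variables with no composite, order of testing or rule for success. Intelligibility, the first thing the hypothesis names, is not among the eight perceptual categories listed, and the text does not say whether general impression contains it. The acoustic measures describe pitch, perturbation and noise. They bear on the voice problems that the Protocol also treats, but they are not measures of intelligibility.

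Two things are at stake. First, after the data are in, any of the 33 variables, at any of three post-treatment visits, could be presented as the primary result, and the Protocol gives no ground for preferring one to another. Second, the sample size rests on one effect for one unnamed outcome, so it does not match a primary outcome made of 33 variables.

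**Working it through.** **Inputs.** From the Protocol: 21 perceptual dimensions; 6 acoustic measures; 2 speech materials; effect size 1.08; 20 per group from the power analysis; 60 planned (30 per group); attrition about 25%. Assumed, because the Protocol is silent: two-sided alpha of 0.05, one between-arm test per variable, and equally correlated normal test statistics for the error calculation.

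**Step 1: reproduce the Protocol's own figure.** For a two-sample t comparison at d = 1.08 and two-sided 0.05, 90% power needs 19.03 per group, rounded up to 20, which is 40 in total as stated. (80% power would need 14.5, rounded up to 15.) Power at exactly 20 per group is 91%. The stated size therefore fits one primary comparison at about 90% power.

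**Step 2: count the primary variables.** 21 + 6 × 2 = 33. If the two speech materials are not counted separately, 21 + 6 = 27.

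**Step 3: chance of at least one false positive among the primary variables.** Under independence, for a result in either direction, 1 − 0.95^33 = 1 − 0.184 = 82%. For a result favouring active tDCS, each test has a 2.5% chance, so 1 − 0.975^33 = 1 − 0.434 = 57%. With a common correlation ρ, the either-direction chance is 1 − E[{Φ((1.96 − √ρ·Z)/√(1−ρ)) − Φ((−1.96 − √ρ·Z)/√(1−ρ))}^33] over a standard normal Z, evaluated numerically. The one-direction version drops the second Φ term.

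| Common correlation | Either direction (nominal 5%) | Favouring active tDCS (nominal 2.5%) |
|---|---|---|
| 0 | 82% | 57% |
| 0.3 | 69% | 37% |
| 0.5 | 53% | 27% |
| 0.7 | 35% | 18% |
| 0.9 | 18% | 9% |

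With 27 variables, the either-direction figures are 1 − 0.95^27 = 75% under independence and 48% at 0.5. The table counts one test per variable and leaves out the multiple visits.

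**Step 4: cost of keeping all 33 primary with Bonferroni.** The per-test alpha is 0.05/33 = 0.0015. Power for any one variable at d = 1.08:

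| Evaluable per group | alpha 0.05 | alpha 0.0015 |
|---|---|---|
| 20 (power-analysis minimum) | 91% | 51% |
| 22 (60 × 0.75 = 45, so 22 per group) | 94% | 58% |
| 30 (no attrition) | 98% | 80% |

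Reaching 80% at the Bonferroni level needs 30.2, that is 31 evaluable per group, which is more than the 30 per group to be randomised.

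**The case against.** The strongest reply is that only the Protocol is at hand. The multiplicity method and the exact ANOVA contrast are commonly left to a SAP, and Statistical analyses neither rules out adjustment nor says what counts as success. This stands. A reader might infer that the plan has no error control, or that any single p-value below 0.05 would be declared efficacy. The document says neither, and the point does not rest on them. It rests on what the Protocol itself fixes as primary.

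A reader might also infer that a positive trial is likely by chance. The figures do not support that. The hypothesis is directional, and false positives favouring active tDCS exceed 50% only near independence. Independence is implausible here: jitter and RAP both measure frequency perturbation, and the same six measures come from two tasks by the same speaker.

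The hypothesis also covers speech-related physiological functions, and the Protocol lists phonatory symptoms and provides voice rehabilitation, so the acoustic measures are relevant to the trial. That stands too. It supports keeping them in the study, but it does not make them tests of intelligibility.

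Finally, the Protocol provides for one consensus rating. That resolves disagreement among the five raters; nothing says that it combines the 21 dimensions into one score.

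**Conclusion.** The point holds as a primary outcome fixed badly in the Protocol: 33 variables (27 on the narrower count) stand under one primary heading, and no variable, visit or between-arm contrast is designated for the intelligibility part of the hypothesis. The inflation is real but its size depends on a correlation that the documents do not give. It runs from 18% to 82% in either direction against 5%, and from 9% to 57% in favour of active tDCS against 2.5%, for common correlations from 0.9 down to 0. Even at the high end of correlation it is more than three times nominal. These figures assume one two-sided 5% test per variable and no adjustment in a SAP.

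An adjustment added later would not repair the design by itself. With all 33 kept primary under Bonferroni, power at the Protocol's own effect is 58% at the numbers expected after attrition. With one designated test it is 94%.

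**What to change.** Before any outcome data are seen, amend the Protocol to designate:

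1. One primary variable from the planned perceptual ratings that represents intelligibility. The Protocol must say which item of the scale this is, for example one within general impression.
2. One primary visit, for example the assessment immediately after treatment. Since the aim covers short- and long-term effects, the investigators should give the reason for their choice.
3. The between-arm contrast: either the group-by-time interaction or the baseline-adjusted group difference, at two-sided 5%.

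Make the other perceptual dimensions, the acoustic measures and the other visits secondary or exploratory, and state the expected direction for any confirmatory secondary. The multiplicity method for the secondaries can be left to the SAP.

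The cost is wording. With one test at two-sided 5%, the stated 20 per group remains adequate at d = 1.08, and no extra participants are needed. No new data are needed either, provided that the scale contains an item for intelligibility, which the Protocol does not show and the investigators must confirm. The downside is that a result on another dimension or visit can no longer be claimed as primary.

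### F0 level is listed as a primary acoustic measure with no direction of benefit, so a shift in its average does not show improvement

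*Protocol*

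**What the plan says.** In the protocol, the section Perceptual and acoustic speech assessments stands under the heading Primary outcome measure. Its acoustic list begins "Acoustic measurements will include fundamental frequency (F0), variability of fundamental frequency (vF0), frequency perturbation (jitter" and continues "intensity perturbation (shimmer %), relative average perturbation (RAP), and noise to harmonic ratio (NHR) to be obtained from both sustained vowel phonation and connected speech". F0 appears beside a separate entry for its variability, so the natural reading is that F0 means pitch level.

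The same primary heading holds the perceptual ratings, whose "scales include 21 speech dimensions covering eight categories, including pitch, loudness, voice quality, resonance, rate, articulation, tone, and general impression".

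The section Statistical analyses states: "Two-way repeated-measures Analyses of Variance (ANOVAs) will be applied for each dependent variable". With two groups and four assessments, the two factors are presumably group and time.

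Three other sections bear on how a change in F0 would be read:

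- The background says "Dysarthric speech may sound mumbled, choppy, soft, slurred, slowed but rushed, with abnormal pitch and rhythm". This gives no direction for the pitch abnormality.
- The hypothesis is that stimulation "would result in increased speech intelligibility and speech related physiological functions". It predicts nothing for F0.
- For therapy, "The treatment targets will be chosen based on the speech assessment results", so targets may differ between participants.

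The protocol gives no target, norm, deviation score or direction of benefit for F0.

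**The concern.** Jitter, shimmer, RAP and NHR measure perturbation or noise, so a fall can be read as improvement. F0 level cannot be read this way: a voice that is too low improves by rising, and one that is too high improves by falling. A group-by-time test on F0 as listed asks whether average pitch moved differently in the two arms. The trial asks whether speech got better.

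Two errors could follow. A real normalising effect could be missed because corrections in opposite directions offset each other. Or a significant mean shift could be reported as an effect on a primary outcome although it is not improvement, and although some participants may have moved away from their normal pitch. The second error needs no cancellation at all.

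The problem is separate from the difference in F0 between men and women. It remains within one sex and on a semitone scale.

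**Working it through.** **The plan's own figure.** The section Participants gives an effect size of 1.08 and 20 per group, without alpha or power. Assuming a two-sided t-test at alpha 0.05, the noncentral t distribution with 2n − 2 degrees of freedom and noncentrality 1.08 × √(n/2) gives power of 90.0% (just below, 0.8995) at n = 19 and 91.4% at n = 20. So 20 is the smallest group size that reaches 90%. (One-sided alpha 0.05 with 95% power also gives 20.) The figure reproduces. It is used below only to set the scale.

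**Offsetting, on the planning effect.** Assumptions that are not in the protocol: the 1.08 SD effect applies to F0, and a share q of participants improves by moving downward. The mean effect on F0 is then

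(1 − q) × 1.08 − q × 1.08 = 1.08 × (1 − 2q).

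Simulated power (20,000 trials, 20 per arm, two-sample t-test on change):

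| q | Net effect (SD) | Power on F0 change | Power if each change is aligned to that participant's direction of benefit |
|---|---|---|---|
| 0 | 1.08 | 91% | 91% |
| 0.1 | 0.86 | 67% | 91% |
| 0.2 | 0.65 | 41% | 91% |
| 0.3 | 0.43 | 20% | 92% |
| 0.4 | 0.22 | 9% | 91% |
| 0.5 | 0 | 5% | 92% |

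The last column is a yardstick, not an available analysis, because the true direction for each participant is unknown.

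**Offsetting, on a semitone model.** Assumptions, again not in the protocol: deviation from the participant's normal pitch averages 3 semitones (SD 1), visit noise is 0.8 semitone, and recovery is 50% with active and 20% with sham stimulation. A share s of participants is too low. The expected difference between arms is (0.50 − 0.20) × 3 × (2s − 1) = 0.9 × (2s − 1) semitones.

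| s | Expected difference (semitones) | Power on F0 change |
|---|---|---|
| 0.5 | 0 | 5% |
| 0.7 | 0.36 | 12% |
| 0.9 | 0.72 | about 38% |
| 1.0 | 0.90 | 64% |

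**Would distance from a reference repair it?** In the same semitone model, take as outcome the absolute distance from one population reference, and let each speaker's own normal F0 vary around that reference (also an assumption). Power hardly depends on s, but it falls with that spread:

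| SD of personal normal F0 (semitones) | Power on distance |
|---|---|
| 0 | 63% |
| 1 | 53% |
| 2 | about 31% |
| 3 | 18% |

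The reason shows in one case. A speaker whose own normal is 3 semitones below the reference and whose voice is raised by 3 sits on the reference, at distance 0. Recovering half the deviation puts that speaker 1.5 semitones below it, so the distance rises from 0 to 1.5 and a recovery is scored as worsening.

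**The case against.** The strongest reply is that the protocol never says the F0 value is raw, signed or a mean. How a variable is derived is commonly left to an analysis plan, and that plan is not shown. This stands in part: a reader might infer that the protocol fixes a signed raw mean, but that is only the natural reading of a bare list followed by an ANOVA for every variable. It does not dispose of the point. The protocol itself names F0, places it under the primary outcome and names the test, and what counts as benefit is part of defining a primary outcome.

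Second, nothing in the protocol says that some participants will be too high and others too low. Individual therapy targets do not establish it either, since they are described only as speech drilling and voice rehabilitation. This stands. A reader might infer that opposite improvements will cancel; the documents support only that they can. With one common direction there is no loss, and the loss is complete only at an even split.

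Third, F0 is one variable among many under the primary heading, and the hypothesis does not rest on it. This stands as well. The point does not extend to jitter, shimmer, RAP, NHR or the perceptual ratings, and it is no ground for saying that the analysis as a whole fails to measure improvement.

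Fourth, a distance-from-reference score brings its own mis-scoring. The last table confirms this.

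**Conclusion.** The point holds for F0 level only. As listed and tested, F0 has no better or worse direction, so neither a significant nor a null result on it would answer whether speech improved. That conclusion needs no numerical assumption.

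The possible loss of power is conditional. It runs from none, if all participants need the same shift, to complete, at an even split; a minority of 10% to 20% already lowers power from 91% to between 67% and 41% under the first model. These figures rest on an assumed effect on F0, and in the second model on assumed deviation, noise and recovery. The true mix of directions cannot be taken from the protocol. The matter deserves correction before the data are analysed, but it does not undermine the other primary measures.

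**What to change.** Take F0 level out of the primary efficacy set and report it descriptively by arm and visit. Leave improvement in pitch to the perceptual pitch dimensions already under the primary heading, and state that these are scored as degree of deviation, since the protocol does not describe the scale's anchors. Jitter, shimmer, RAP and NHR stay as they are.

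The cost is a short change of wording and one fewer primary acoustic variable. No new recording or external norm is needed.

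If a distance-from-reference score is wanted, keep it as a supportive analysis at most. Use a sex-specific reference fixed before unblinding, and acknowledge that natural differences in normal F0 between speakers can mis-score recovery and reduce power substantially.
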